## Abstract

**Background:**

Heart failure remains a leading cause of mortality and a major driver of health care utilization. Despite numerous medical advances in heart failure, associated hospitalizations continue to increase, owing largely to suboptimal outpatient management. Remote patient monitoring (RPM) aims to further address this current need in heart failure care by providing data to clinical teams to act pre-emptively to address clinical decompensation. However, to date, RPM approaches using noninvasive home-based patient sensors have failed to demonstrate clinical efficacy.

**Objective:**

The Novel Data Collection and Analytics Tools for Remote Patient Monitoring in Heart Failure (Nov-RPM-HF) Trial aims to address current noninvasive RPM limitations. Nov-RPM-HF will evaluate a clinician co-designed RPM platform using emerging data collection and presentation tools for heart failure management. These tools include a ballistocardiograph to monitor nocturnal patient biometrics, clinical alerts for abnormal biometrics, and longitudinal data presentation for clinician review.

**Methods:**

Nov-RPM-HF is a 100-patient single-center prospective trial, evaluating patients over 6 months. The outcomes will include patient adherence to data collection, patient/clinician-perceived utility of the RPM platform, medication changes including the titration of guideline-directed medical therapy to target doses, heart failure symptoms/performance status, and unplanned heart failure hospitalizations or emergency department visits.

**Results:**

This prospective trial began enrollment in March 2020 and anticipates enrollment completion by June 2022, with trial completion by December 2022.

**Conclusions:**

This trial protocol aims to provide a systematic framework for the evaluation of heart failure RPM strategies, which are currently heavily used but seldom robustly studied. The trial results will help to inform the role of noninvasive RPM as a viable clinical management strategy in heart failure care.

**International Registered Report Identifier (IRRID):**

DERR1-10.2196/32873

## Introduction

Heart failure (HF) remains a leading driver of morbidity and mortality in the United States, affecting 6.5 million Americans [1]. Despite numerous medical innovations in HF over the past decade, per capita rates of HF hospitalizations have actually increased from 2010 to 2017 [2]. This population is expected to increase by 50% by 2030, placing an increasing burden on the US health care system and highlighting the need for innovations in HF care [3]. HF care also carries significant economic implications, with over US $30 billion spent in direct HF care in 2020, primarily driven by HF hospitalizations, and estimated to double by 2030 [4-6].

Effective HF care requires vigilance for indications of clinical HF decompensation. Failure to detect and manage these indicators can result in unplanned emergency department (ED) visits and hospitalizations. Although patients and care teams attempt to detect signs of impending decompensation with conventional techniques such as daily weight measurements, these approaches have not demonstrated consistent clinical efficacy [7].

Optimal HF care also relies on maximizing guideline-directed medical therapies (GDMTs). Several pharmacotherapies such as renin-angiotensin-aldosterone system inhibitors and beta-blockers have demonstrated mortality benefit in patients with HF with reduced ejection fraction (HFrEF) [8,9]. However, consistent provision of these therapies, at maximally tolerated dosing, does not occur [10]. Logistical challenges of conventional outpatient care contribute to this implementation gap. These include reliance on ambulatory visits for medication titration, which often occur months apart, and insufficient vital sign information to allow for medication up-titration between visits.

Remote patient monitoring (RPM) aims to address these gaps in current HF care. RPM is a strategy that allows care teams to monitor and manage patients outside of traditional in-person health care encounters. The strategy could enhance current efforts for more rapid medication titration and avoidance of clinical decompensation and unplanned acute care visits. RPM has demonstrated a reduction in HF hospitalizations, but only by using an invasive hemodynamic patient sensor (CardioMEMS) [11]. RPM strategies using noninvasive patient sensors such as blood pressure (BP) cuffs, scales, and wearable biosensors have reduced cost, lower risk, and greater applicability to the HF population. However, the clinical evidence supporting noninvasive RPM is mixed, with the majority of clinical trials failing to demonstrate a similar clinical benefit [12]. This lack of clinical efficacy in trials is likely attributable to multiple factors, including poor patient adherence [13], lack of clinically actionable patient data and alerts [14], and lack of clinician engagement [15].

The field of noninvasive RPM continues to evolve, with recent advances in data collection and monitoring now demonstrating improved predictive power for clinical decompensation [16]. However, there is a paucity of studies evaluating these emerging tools as part of RPM interventions.

The Novel Diagnostic Tools for Remote Patient Monitoring in Heart Failure (Nov-RPM-HF) Trial aims to address these limitations through the design and evaluation of a novel RPM platform for HF management that incorporates these emerging data collection tools. The trial will evaluate the perceived utility of the RPM platform, its impact on timely GDMT optimization and medication changes, and its impact on unplanned ED visits and hospitalizations.

## Methods

### Overview

The Nov-RPM-HF trial is a single-center prospective study of an RPM platform and its adoption, clinical utility, and ability to optimize GDMTs and reduce unplanned acute care events among patients with HFrEF. Specifically, the trial will evaluate patient adherence with passive and active data collection, patient-perceived usability and utility of the RPM platform to monitor their health status, clinician-perceived usability and utility of the RPM platform for HF management, clinical utility of the RPM clinical alerts, impact of RPM on medication changes and titration of HF GDMT, and impact of HF RPM on clinical outcomes (ED visits, hospitalizations).

Full inclusion and exclusion criteria are summarized in Textbox 1. Inclusion criteria include history of HFrEF with a HF hospitalization or ED visit in the last 12 months. This criteria selects for a HFrEF population with a baseline event rate that mirrors the trial population in the CHAMPION (CardioMEMS Heart Sensor Allows Monitoring of Pressure to Improve Outcomes in NYHA Class III Heart Failure Patients) trial. Such an event rate should allow for increased power to detect clinical outcomes among our study population. Prior noninvasive RPM trials have included a relatively stable population of patients with HF with low clinical event, and this was thought to have contributed to the inability to demonstrate clinical efficacy [13]. End-stage HF with a life expectancy <1 year or requiring advanced therapies including left ventricular assist devices or cardiac transplantation were excluded. Patients with barriers precluding them from obtaining monitored data (eg, wearable defibrillator use preventing ballistocardiograph sensing) were also excluded.

Inclusion and exclusion criteria.
**Inclusion criteria**
Age≥18 yearsHF (heart failure) hospitalization or emergency department visit in last 12 monthsHF with reduced ejection fraction: most recent left ventricular ejection fraction (LVEF) of <50% and at least 1 recorded LVEF of <40%New York Heart Association Functional Class II-IVSleeps in same bed ≥4 days per weekAmbulatoryWillingness to complete the required surveys, measurements, and study activities
**Exclusion criteria**
Advanced HF therapies: inotrope therapy, left ventricular assist device or cardiac transplantationWearable defibrillator or other worn device that may affect ballistocardiogram measurementsEnd-stage renal disease on chronic dialysisMalignancy undergoing active therapyWeight >385 lbs at time of enrollmentLiving in a skilled nursing facility or other chronic care facilityPlanned major surgeries or procedures requiring hospitalization in next 6 monthsHospice care or life expectancy <1 year

Patients were prospectively screened and recruited from the Advanced Heart Failure clinic at the Washington University School of Medicine’s Division of Cardiology. This clinic specifically treats patients with HF, with a focus on implementation of GDMTs and evaluation for advanced therapies including mechanical circulatory assist devices and cardiac transplantation when indicated. The trial was approved by the institutional review board at Washington University for either written or phone-based informed consent. The trial began recruitment in March 2020.

### Ethical Considerations

The trial was approved by the ethics review board of the Washington University Office of Ethics and Integrity, with all information for patient informed consent reviewed. The trial was deemed to be in equipoise with current standard of care for heart failure management.

### RPM Platform

The RPM platform for the trial was provided by a third-party vendor, Myia Health (San Francisco, CA). The platform consists of patient biometric sensors, a digital “Home Hub” tablet to aggregate data from the sensors and transmit to the vendor for analysis, and a web-based clinical interface for clinicians to review data. The clinical interface was co-designed with the advanced HF clinicians to incorporate clinician priorities in its design. To ensure that the RPM platform was optimally designed for clinician and patient needs, Myia conducted clinician and patient interviews (n=51), and incorporated their input into the design of the RPM platform (Figure 1). These interviews identified the following priorities for the prospective RPM platform: home sensors that collected data with minimal or no actions from the patient, optimizing ease-of -use clinical monitoring platform for clinicians with integration into current workflows, and data curation through smart triaging to minimize information overload for the clinical teams.

The RPM platform (Figure 1):

Patient biometric sensors: Sensors include a weight scale, BP cuff, and a ballistocardiograph. The ballistocardiograph is a pressure-based sensor that is placed under a patient’s bed mattress. It measures ballistic forces related to heart and lung movement to derive heart rate (HR), respiratory rate (RR), and other associated physiologic parameters. Importantly, the ballistocardiograph is always “on” and only requires the patient to lie in bed to collect data, thus minimizing the data collection burden for patients.Home Hub tablet: An Android (Google) LTE-enabled tablet loaded with the Myia application serves as a data aggregation and transmission point for collected vital sign sensor data. It also includes a user interface to solicit, collect, and transmit patient-reported outcomes.Clinical interface: The clinician interface displays sensor data for all patients currently enrolled in the trial. The interface includes a data visualization workspace that juxtaposes longitudinal health data (vital signs, symptoms) with event data (ED visits, hospitalizations) to aid in clinical management. Patient data is prioritized for clinical review using alerts. Alerts are customized based on patient-specific thresholds (eg, vital signs outside of predefined range), with deviations outside normal range triggering an alert. Additionally, among patients on submaximal GDMTs, medication-specific alerts are included to allow for rapid HF medication up-titration.

**Figure 1 figure1:**
[figure not shown]
Remote patient monitoring platform used in the Novel Data Collection and Analytics Tools for Remote Patient Monitoring in Heart Failure Trial. BP: blood pressure; ECG: electrocardiogram.

### Study Protocol

Following enrollment, study participants have the Home Hub and sensors shipped to their homes. Once the kit is delivered, the technical support team will reach out to assist with home monitoring and sensor setup.

As part of the study, patients will take measurements daily from all study sensors. The first 7 days for each patient will be a run-in period where patient data is collected. If sufficient data is collected and transmitted, study participants will transition to the active management phase. Sufficient data is defined as transmission from both BP cuff/weight scale and ballistocardiograph sensors in at least 4 of the 7 days. If minimum requirements are not met, patients are continued in the run-in period for an additional week (up to 3 weeks maximum). Technical support will contact patients to determine if lack of transmission represents a technical issue versus nonadherence. If patients were unable to meet minimum data requirements after 3 weeks, then they were disenrolled from the study.

Following run-in period completion, study participants will enter the 6-month active management phase of the study. A designated research nurse is responsible for daily monitoring of the RPM clinical interface. This includes monitoring the RPM clinical interface daily for clinical alerts, contacting patients to assess clinical status in response to alerts, and escalating to the patient’s HF cardiologist if clinical status warrants management changes. This research nurse will also be responsible for contacting study participants for issues with data transmission or poor adherence to patient data collection.

On a monthly basis, enrolled patients will have their clinical data reviewed by a multidisciplinary team including a triaging nurse and an HF cardiologist. The purpose of these reviews is to assess participant’s clinical status and adherence to data transmissions, and to identify opportunities for optimized medical management, including maximizing GDMT. RPM platform monitoring is outlined in Figure 2.

**Figure 2 figure2:**
[figure not shown]
Remote patient monitoring platform monitoring strategies. BP: blood pressure; GDMT: guideline-directed medical therapy; HF: heart failure; HR: heart rate.

#### Clinical Alerts and Thresholds

Several clinical monitoring alerts will be used prospectively during the management phase of the study. Each alert has default thresholds that are customizable to individual study participants. Absolute threshold alerts will be turned on by default in all patients, while GDMT alerts can be opted-in by the clinical team for patients deemed to be on submaximal GDMT. Default values are shown in Textbox 2. All alerts are required to be addressed within 24 hours by the monitoring nurse and escalated to the clinical team if indicated. Actions taken by the clinical team in response to the alerts were documented.

Remote patient monitoring clinical interface parameters with default values.
**Absolute thresholds alerts**
High and low thresholds for weight, blood pressure (BP), and heart rate (HR). Thresholds include both default absolute values and patient-specific deviation from baseline values.Weight>3 lbs over 1 day>5 lbs over 3 daysBPSystolic blood pressure (SBP)>200 mmHgSBP>180 mmHg each day for 3 consecutive daysSBP<80 mmHgHRHR<35 bpm average in 1 nightHR>150 bpm
**Guideline-directed medical therapy (GDMT) alerts**
These alerts are generated for patients on submaximal GDMT. They are designed to permit rapid up-titration of GDMT, customized based on drug class.Beta-blockerHR>80 bpm (nightly average) and SBP>100 mmHg for 3 consecutive daysAngiotensin-converting enzyme inhibitor, angiotensin receptor blocker, angiotensin receptor neprolysin inhibtor, and mineralcorticoid receptor antagonistSBP>110 for 3 consecutive days

#### Outcomes

Trial outcomes were designed to both directly evaluate the perceived utility of the RPM platform and to assess its impact on clinical outcomes.

##### Patient Adherence to Data Collection and Transmission

Patient data collection adherence will be measured for all home BP cuff, scale, and ballistocardiograph sensors as percentage of days with data transmission from each device over the 6-month trial duration. “Minimally-useful data profile” is defined as the percentage of weeks with at least 4 days of data transmission from both an *active* (BP cuff or weight scale) and *passive* (ballistocardiograph) sensor.

##### Patient-Perceived Usability and Utility of RPM Platform

Patients’ assessment of the RPM platform utility and usability will be assessed through a series of surveys (survey timeline in Multimedia Appendix 1). Surveys will be conducted at 2, 4, and 6 months. Surveys will have scaled numerical responses 1 to 7, with 17 total questions. Questions will assess RPM platform components (scale, BP cuff, ballistocardiograph) usability, platform setup, and the platform’s perceived utility in augmenting clinical care. The sum of the numeric responses for each question will combine into an “overall utility score.” This score will be assessed for change throughout the study duration for each participant. Surveys will be reviewed at the time of submission by the research nursing group. Patients will be contacted regarding any significant RPM platform concerns. Scores will also be analyzed to assess for RPM platform strengths/weaknesses and to evaluate for change in perceived utility over the trial duration.

##### Clinician-Perceived Usability and Utility of RPM Platform

Along with patients, clinicians will also be assessing the RPM platform’s utility and usability through a series of surveys (survey timeline in Multimedia Appendix 1). Surveys will be conducted at 3 and 6 months, with scaled numerical 1 to 7 ratings of 14 components of the RPM platform, with a focus on the clinical interface.

##### Clinical Utility of RPM-Generated Clinical Alerts

The number of absolute threshold clinical alerts (Textbox 2) generated by the RPM platform will be reported, along with its accompanying clinical action. Clinical actions include medication changes (adding/holding medications), scheduling a follow-up appointment, advising immediate medical care (ED visit or hospitalization), or no action. The clinical utility of each absolute threshold alert will be measured as the percentage of clinical alerts prompting clinical action and categorized by physiologic measure (ie, weight, BP, and HR).

##### Medication Changes

Clinician-directed changes will be tracked during trial duration for the following HF medication classes: beta-blockers, angio-converting enzyme (ACE)/angiotensin receptor blocker (ARB)/angiotensin receptor-neprilysin inhibitors (ARNIs), magnetic resonance angiographies (MRAs), hydralazine, nitrates, and loop diuretics. The distance to target dose will also be assessed for GDMT medications, beta-blocker, ACE/ARB/ARNI, and MRA drug classes. Based on previously established methodology [10], baseline doses of each of these drug classes will be the classified percentage of target dose: 0% to 25%, 25% to 50%, 50% to 75%, and 75% to 100%. This target dose category will be compared for each participant between 0 and 6 months to assess for changes in GDMT dosing. Change in proximity to target dose over trial duration will be compared to that of matched controls (see “Statistical Considerations” for matching methodology). For all drug classes, the absolute number of medication changes will be recorded and compared to that of the matched controls.

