#### Statistical Analysis

Patient medication changes and clinical events will be compared to 100 matched historical controls. Controls will be patients with HFrEF matched on an HF hospitalization in the past year, age within 5 years, sex, race, and comorbidities (coronary artery disease, diabetes mellitus, hypertension, renal disease).

Statistical analysis for clinical end points will be in comparison with matched controls. For survey data, including RPM platform utility and patient symptom assessments, these will be evaluated for change over the trial’s 6-month duration. Continuous variables will be assessed via sample *t* tests, and categorical variables will be assessed via chi-square tests.

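### The GDMT dose bands share edges and have no separate level for untreated or at target, and the only test given for categories ignores pairing and order

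*Protocol article*

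**What the plan says.** Under Outcomes, Medication Changes, the protocol article assesses distance to target dose for beta-blockers, ACE/ARB/ARNI and MRA. It cites an established method and bands the baseline dose of each class: "classified percentage of target dose: 0% to 25%, 25% to 50%, 50% to 75%, and 75% to 100" percent. The band is then used within patients: "This target dose category will be compared for each participant between 0 and 6 months to assess for changes in GDMT dosing". There is also a between-group comparison: "Change in proximity to target dose over trial duration will be compared to that of matched controls". A second, separate measure is a count: "For all drug classes, the absolute number of medication changes will be recorded and compared to that of the matched controls".

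Under Statistical Analysis, controls are matched on an HF hospitalization in the past year, age within 5 years, sex, race and four comorbidities. Baseline dose is not on that list. Two general rules name the tests: "Continuous variables will be assessed via sample *t* tests", and "categorical variables will be assessed via chi-square tests". Neither rule names the dose-band outcome. The trial has 100 patients and 100 matched historical controls.

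**The concern.** Bringing drug therapy to target dose is one of the outcomes named in the abstract and one of the aims in the Overview. Three features of the dose outcome work against measuring it.

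- **Bands.** A dose on an edge can be scored two ways. The two end states of most interest, not on the drug and at target, have no level of their own.
- **Within-patient test.** The same participant is read twice on an ordered scale. An ordinary chi-square uses neither the pairing nor the order.
- **Control comparison.** A patient already in the top band cannot move up. If trial patients and historical controls start at different doses, they differ in room to improve, and nothing stated removes that difference.

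At stake are a real dose improvement that is missed, a result that depends on an edge convention, and a control contrast partly driven by starting dose.

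**Working it through.** The article states no power or sample size for this outcome, so there is no figure to reproduce.

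**1. Band scoring.** The ladder 0, 12.5, 25, 50, 100% of target is an assumption; the article gives none. Bands are numbered 1 to 4.

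| Step | Edge dose goes to upper band | Edge dose goes to lower band |
|---|---|---|
| 0 to 12.5% | 1 to 1, change 0 | 1 to 1, change 0 |
| 12.5 to 25% | 1 to 2, change 1 | 1 to 1, change 0 |
| 25 to 50% | 2 to 3, change 1 | 1 to 2, change 1 |
| 50 to 100% | 3 to 4, change 1 | 2 to 4, change 2 |

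A start below 25% never registers, and a start at exactly 25% registers under one convention only. Off this ladder, a rise from 75% to 100% is hidden if 75% is placed in the top band, and a rise from anywhere above 75% to 100% is hidden under both conventions. A start above 25%, or a rise from 50% to 100%, does change band.

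**2. Within-patient test, one cut-point.** Assumed inputs: 40% above a cut at baseline; 25% of those below move up; 6% of those above move down.

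- Up: 0.60 × 0.25 = 0.150. Down: 0.40 × 0.06 = 0.024. Net change: 0.126, so 40% becomes 52.6%.
- True variance of the paired difference, per patient: (0.150 + 0.024) − 0.126² = 0.158.
- Variance used by chi-square, with mean proportion 0.463: 2 × 0.463 × 0.537 = 0.497.
- At n=100, chi-square works with a standard error of √(0.497/100) = 0.0705, where the true one is √(0.158/100) = 0.0398. Its approximate power is 1 − Φ[(1.96 × 0.0705 − 0.126)/0.0398] = 1 − Φ(0.31) = 0.38.

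Simulated power (20,000 runs, uncorrected chi-square, two-sided 0.05):

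| n | Up / down | Exact McNemar | Chi-square |
|---|---|---|---|
| 90 | 25% / 6% | 0.81 | 0.30 |
| 100 | 25% / 6% | 0.86 | 0.40 |
| 100 | 40% / 6% | 0.996 | 0.96 |

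Repeated runs of the first row vary between 0.81 and 0.82 for McNemar. With no net change (8% up, 12% down: 0.40 × 0.88 + 0.60 × 0.08 = 0.40), chi-square rejected in about 0% of runs.

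**3. Within-patient test, four bands.** Assumed inputs: n=100; baseline shares 35, 25, 20 and 20%; moves of one band; 2,000 runs.

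| Up / down | Paired sign test | 2×4 chi-square, times as independent |
|---|---|---|
| 20% / 5% | 0.83 | 0.00 |
| 25% / 8% | 0.82 | 0.00 |
| 30% / 10% | 0.89 | 0.02 |
| 30% / 5% | 0.99 | 0.02 |

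With 15% up, 15% down and equal baseline shares, the 2×4 chi-square rejected in 0.0% of runs and the sign test in 3.0%. A 4×4 chi-square of baseline band by 6-month band rejected in 100% of runs with no net change, because it tests association and not change.

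**4. Room to move.** Suppose, as an assumption, that 25% of those below the top band move up in both groups. The share moving up is 0.25 × (1 − top-band share). Top-band shares of 20% and 40% give 0.25 × 0.80 = 20% and 0.25 × 0.60 = 15%, a difference of 5 points with no effect of monitoring. With equal shares the difference is 0.

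**The case against.** A reader might infer that starting a drug and reaching target are invisible. The article does not support that. Starts above 25% and moves from 50% to 100% change band under either convention. The separate medication-change count should also pick up starts, since the section on clinical alerts lists adding a medication among medication changes. That count is also the medication measure for which power is stated. It does not show distance to target, however, and it mixes in loop diuretics, nitrates and hydralazine.

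A reader might also infer that the article prescribes an unpaired chi-square for the 0-to-6-month comparison. It does not say so. The rule is general, and a condensed article may leave the exact test to an analysis plan that is not shown. A chi-square on moved up, yes or no, between groups would not commit the pairing error described: with 15% in both groups of 100, treated as independent, it rejected in 4.8% of simulations. What stands is that chi-square is the only test given for categorical data, and that it does not suit the paired, ordered comparison the article describes.

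The bands follow a cited source, which may define the edges or separate 0% and 100%. The article also does not say that exact percentages are discarded. Neither point repairs the printed definition.

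Finally, the power figures rest on assumed movement rates, and the loss nearly vanishes when many patients move. No baseline-dose imbalance with the controls has been shown; it is a risk that the stated design leaves open.

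**Conclusion.** The point holds at moderate severity. Certain from the text: the bands share three edges; untreated and at-target patients have no separate level; the within-patient comparison is paired and ordered; and baseline dose is neither matched on nor adjusted for in what is stated.

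Inferred: that the general chi-square rule would be applied to this outcome. If it were, with the two times treated as independent, the error would be towards missing change. No inflation of false positives is shown for that test. The loss ranges from near-total in the four-band scenarios, through 0.30 against 0.81, to 0.96 against 0.996, depending on the movement assumed.

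The outcome is neither the primary clinical end point, which is HF hospitalization, nor one for which power is stated. No figure in the article changes.

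**What to change.** 1. Analyse the actual percentage of target dose for each class, as a continuous or ordinal measure.
2. Compare with matched controls on the 6-month value, adjusted for the baseline value.
3. Test within-patient change with a paired method: Wilcoxon signed-rank for the percentage, or McNemar/Bowker if categories are kept.
4. For display, use mutually exclusive bands with a stated edge rule, and show not on drug and at target or above as separate levels.

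The doses must already be obtained to assign the bands, so no new data are needed. The cost is outcome and analysis wording plus slightly more analysis work, and it should be settled before the data are analysed.

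### Change in target-dose category is compared in all patients and controls, including those already in the top band, and baseline dose is not matched, so the contrast is diluted and can be biased

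*Protocol article*

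**What the plan says.** All references are to the protocol article.

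- **Objective.** The Overview lists "impact of RPM on medication changes and titration of HF GDMT" among the aims.
- **Outcome.** Under Medication Changes, baseline dose in the beta-blocker, ACE/ARB/ARNI and MRA classes is sorted into bands of "0% to 25%, 25% to 50%, 50% to 75%, and 75% to 100" per cent of target. Then: "This target dose category will be compared for each participant between 0 and 6 months to assess for changes in GDMT dosing". And: "Change in proximity to target dose over trial duration will be compared to that of matched controls". Neither sentence restricts the comparison to patients with room to rise.
- **Eligibility.** The criteria cover ejection fraction, a recent HF event and functional class among other things. Neither list mentions GDMT dose.
- **Recruitment.** The source is an advanced HF clinic: "This clinic specifically treats patients with HF, with a focus on implementation of GDMTs and evaluation for advanced therapies".
- **Intervention.** Clinical Alerts and Thresholds says "GDMT alerts can be opted-in by the clinical team for patients deemed to be on submaximal GDMT". RPM Platform and the GDMT section of Textbox 2 also tie these alerts to submaximal therapy.
- **Controls.** Statistical Analysis names 100 historical controls matched on HF hospitalization in the past year, age, sex, race and four comorbidities. Baseline dose is not among the factors.

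**The concern.** On the four-band scale, a patient who starts a class in the top band can only stay or fall. Averaging such patients with those who can rise has two consequences.

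1. **Dilution.** The difference between groups shrinks in proportion to the share at the ceiling. The reported effect then reflects the case mix as well as what monitoring does for patients who can be titrated.
2. **Bias.** The controls are historical and not matched on dose, so the ceiling share may differ between groups. A group with fewer patients at the ceiling will show more upward movement even if monitoring does nothing. The direction cannot be known in advance.

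The second consequence is the more serious, because a larger sample would not remove it. At stake is the reading of the GDMT-optimization result, one of the trial's named aims.

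**Working it through.** **Inputs from the article:** 100 patients, 100 controls, type I error 0.05 (taken as two-sided), four dose bands, no matching on dose.

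**Assumed, because not given:** the ceiling share f, the effect among patients with room to rise, and the share of those patients who move up.

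**1. The plan's own figure.** Power Calculation states 99% power for 50% more medication changes, under a Poisson distribution. With log rate ratio ln 1.5 = 0.4055 and SE = √(1/(100λ) + 1/(150λ)):
- λ = 1061/280 = 3.79 changes per control: SE 0.0663, 0.4055/0.0663 = 6.11, power above 99.9%.
- Half that rate, λ = 1.89 (assumed): SE 0.0938, 0.4055/0.0938 = 4.32, power 99.1%.

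The stated figure is reproduced in substance, although the article does not give the control rate it used. It concerns the count of changes in all tracked classes, including loop diuretics, hydralazine and nitrates. No power is stated for proximity to target dose.

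**2. Dilution.** If a share f in both groups cannot rise and shows no effect, the all-patient difference is (1−f) times the difference among the rest.

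**3. Power on a continuous scale.** Assume an effect of 0.5 SD among patients below the ceiling. Let v be the variance of change in ceiling patients relative to the others. Using the normal approximation:
- Restricted: noncentrality = 0.5·√(50(1−f))
- All patients: noncentrality = 0.5·√50·(1−f)/√((1−f)+f·v)
- Power = Φ(noncentrality − 1.96)

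| f | Restricted | All, v=0 | All, v=0.25 | All, v=1 |
|---|---|---|---|---|
| 20% | 88% | 88% | 87% | 81% |
| 40% | 78% | 78% | 72% | 56% |
| 60% | 61% | 61% | 48% | 29% |

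At v=0 (ceiling patients never change dose) the two formulas are identical and restriction gains nothing. v=1 is a worst case, because patients who can only stay or fall are unlikely to vary as much as the others.

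**4. Power on a binary scale.** Assume that, among patients with room, 20% of controls and 40% of monitored patients move up a band.

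| f | All patients, 100 per group | Power, all | Restricted, per group | Power, restricted |
|---|---|---|---|---|
| 0% | 20% vs 40% | 88% | 100 | 88% |
| 20% | 16% vs 32% | 76% | 80 | 79% |
| 50% | 10% vs 20% | 51% | 50 | 59% |

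Most of the loss comes from having fewer informative patients, which a restricted analysis does not recover.

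**5. Bias with no true effect.** Let patients with room rise by m bands on average in both groups, and let ceiling patients not change. With ceiling shares f₁ (monitored) and f₀ (controls), the expected difference is m(f₀ − f₁).
- m = 0.3, f₁ = 20%, f₀ = 40%: 0.3 × 0.20 = 0.06 band in favour of monitoring. Exchanging the shares gives 0.06 against.
- Binary version, 20% of those with room moving up in both groups: 0.20 × 0.80 = 16% against 0.20 × 0.60 = 12%. SE = √(0.16×0.84/100 + 0.12×0.88/100) = 0.049, z = 0.04/0.049 = 0.82. A two-sided 5% test then rejects with probability P(Z > 1.14) + P(Z < −2.78) = 0.126 + 0.003, about 13%.
- Restricted to patients below the top band: 20% against 20%, so rejection stays near 5%, provided the mix of lower bands is similar or adjusted for.

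**The case against.** The case on the other side has real weight.

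- **The ceiling share may be small.** A reader might infer from "with a focus on implementation of GDMTs and evaluation for advanced therapies" that many patients start at target. The article does not say so. Its Introduction says maximally tolerated dosing is not consistently provided, and a patient at the ceiling in one class may have room in another. This stands: the size of the problem is unknown.
- **Titration is not confined to alert patients.** One might infer that monitoring can act on dosing only in submaximal patients. That is true of the GDMT alerts. However, Study Protocol gives every enrolled patient a monthly multidisciplinary review that covers GDMT optimization. This stands. It does not help a patient who cannot move up a band.
- **No stated power is overturned.** The 99% figure is for the count of medication changes. This stands.
- **Restriction buys little power.** This stands at low shares, as steps 3 and 4 show.
- **All-patient net change is a legitimate quantity.** Down-titration is part of the net effect on dosing, and it counts in controls too, so it is not one-sided against monitoring. This stands, and is why that analysis should be kept.
- **Restricting to patients below target would miss the mark.** Someone at 80% of target is below target yet already in the top band. This stands, so the restriction should be set at the band. Patients at their maximum tolerated dose in a lower band would still be included; baseline dose alone cannot identify them.
- **An unseen analysis plan could define a subset.** It could add one. The article does not leave the point open, however: it names each participant and a comparison with the matched controls, and it fixes matching factors that omit dose.

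**Conclusion.** The point holds as a moderate one about how the target-dose comparison is fixed. As written, the contrast is diluted by the share of patients in the top band and is biased if that share differs between monitored patients and historical controls. Both follow from the bands and the matching list. Their size rests on assumptions: a 20% ceiling share scales the difference by 0.8, and a 20-point imbalance in ceiling shares raises false positives from 5% to about 13% in the example above.

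The documents do not support the stronger reading that the GDMT aim is largely lost or that the trial's stated power fails. The reason to change the analysis is interpretability and control of bias. Any gain in power is secondary and may be nil.

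**What to change.** In Medication Changes:

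1. Within each of the three drug classes, make the main proximity-to-target comparison in participants and controls who are below the 75-100% band for that class at baseline. Adjust for baseline dose category and the matching variables.
2. Keep the all-patient net change, including down-titration, as a supportive analysis.
3. Report the percentage in the top band at baseline, by group and by class, so that any imbalance is visible.

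The article already has baseline dose classified by class, so this changes analysis wording only. Recruitment and patient management are untouched. The cost is fewer patients per class in the main comparison and some matched pairs losing a member, which is why adjustment for the matching variables replaces strict pairing.
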